#### Implementation Phase

2.6.3

Implementation of Safewards at each site will occur over 12 weeks. The clinical educator from the aged care organisation and two trainers from the project team (one staff with lived experience of caring for a family member with dementia) will provide on‐site training of aged care staff. An online community of practice groups will be established to share learnings and support implementation across sites.

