#### Evaluation Phase

2.6.4

Programme evaluation will examine the impact of Safewards in aged care homes, and identification of successful implementation strategies and adaptations made to the interventions for service fit. Further details of the outcomes evaluation are provided in Table 3.

**Table 3 hex70037-tbl-0003:** Evaluation summary.

**RE‐AIM domains**	**Evaluation aims and outcome measures**
*Reach:* Participation in the intervention (individual level)	*Aim*: To describe the number, proportion and characteristics of staff who are willing to participate in the intervention. *Data collection: Quantitative*—Number of staff who engaged in the training and participant characteristics (age, gender, qualifications and cultural background).
*Effectiveness*: Impact of the intervention (individual and setting level)	*Aim:* To determine the appropriate and feasible effectiveness outcome measures and potential signals of effect. 1. *Resident outcomes. Data collection: Quantitative*—Pre‐ and postquarterly reports of pro‐re‐nata psychotropic medication use, pre‐ and postquarterly reports of incidents of mechanical, physical and environmental restraint. *Qualitative*—Interviews postimplementation to understand the experiences of the intervention. 2. *Family member outcomes. Data collection: Qualitative*—Interviews postimplementation to understand experiences of the intervention. 3. *Staff outcomes. Data collection: Quantitative:* Pre‐ and postsurveys to assess levels of confidence and capacity to support residents with complex needs and use the intervention, pre‐ and postsurveys to assess staff well‐being. *Qualitative*—Focus groups (or interviews) to understand experiences of the intervention.
*Adoption:* Degree of uptake of intervention (individual and setting level)	*Aim:* To describe the number, proportion and representativeness of staff and settings who delivered the intervention. *Data collection: Quantitative*—Setting exclusions/inclusions (% units and reasons); staff exclusions/inclusions (% of staff invited that participate in training); degree of implementation of Safewards (number of interventions implemented). *Qualitative*—Focus groups (or interviews) to understand staff perceptions of barriers and enablers to setting‐ and staff‐level adoption.

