**Quantitative Data**
1.Routinely collected data pertaining to pro re nata (PRN) psychotropic medication use (from the organisation's psychotropic register where nursing staff record PRN psychotropic medication) and inappropriate restrictive practice incidents (as reported via the Serious Incident Reporting Scheme‐SIRS) will be collected by staff from the aged care organisation and forwarded to the research team for analysis. The total number of PRN psychotropic medications used and restrictive practice events on each individual resident will be calculated over three time periods, which are (1) 12 months before the implementation of the Safewards programme; (2) from start to completion of the programme (3 months) and (3) 3‐months post the completion of the programme. The average use of PRN psychotropic medications for each individual resident per time period, and the total number of restrictive practice events per individual resident per period will be calculated. The difference between the medication usage and a number of events before and after the implementation of the programme will be analysed using the analysis of variance method. The Australian Aged Care Quality & Safety Commission govern the SIRS, which aims to identify and prevent abuse and neglect among people receiving aged care. As only ‘inappropriate’ restrictive practice use is reportable to SIRS, and there is a very low reporting rate sector wide (e.g., < 200 reports of inappropriate restrictive practice use across the entire Australian RAC sector in the October–December 2023 quarter), these data are likely to be limited.2.Surveys (preimplementation and 1 month postimplementation) exploring staff confidence, motivation and uptake of nonrestrictive practices will be forwarded to all aged care staff (*n* = 200). Surveys have been adapted from the Victorian trial (Appendix S2). All data will be de‐identified. Staff will be asked to identify site location and provide a unique identifier to allow for pre‐ and postdata to be combined. Comparisons will be made pre‐ and post‐Safewards implementation. The online platform Qualtrics will be used to collect survey data.3.Routinely collected data pertaining to resident satisfaction with care and quality of life is routinely collected by the organisation for reporting purposes (https://www.qol-acc.org/). The most recent survey data available before the intervention and at the completion of implementation phase will be used for analysis.4.Routinely collected data pertaining to staff satisfaction (from a staff satisfaction survey developed by Willis Towers Watson) and staff injury (via the Injury Management platform). All data will be de‐identified by staff working in the aged care organisation. The most recent survey data available before the intervention and at the completion of implementation phase will be used for analysis.5.The Victoria Safewards fidelity scale (https://www.safewards.net/managers/evaluation-methods) will be adapted for the setting and completed by two members of the research team on completion of the implementation phase and 3 months postimplementation. The fidelity scale reports on the number and quality of interventions that have been implemented.

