### Ethical Considerations

2.10

Ethics was sought from the Flinders University Human Research Ethics Committee to conduct this study. A waiver for consent was sought for de‐identified data including the following: (1) routinely collected data pertaining to psychotropic medication use and restrictive practice incidents (physical, mechanical and environmental restraint); (2) staff satisfaction surveys and (3) consumer satisfaction and quality of life questionnaires.

Data pertaining to psychotropic medication use will be collected and de‐identified by staff from the aged care organisation via an electronic record and/or the psychotropic register. Restrictive practice incidents, documented on internal incident report forms, will be collected and de‐identified by organisational staff. Anonymous staff and consumer satisfaction and quality of life surveys are routinely collected for reporting purposes.

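### The rule for the routine resident and staff surveys does not guarantee a post measure taken after implementation, and can let one wave serve as both pre and post

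*Protocol article*

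**What the plan says.** Section 2.9, Quantitative Data, gives items 3 (resident satisfaction with care and quality of life) and 4 (staff satisfaction) the same timing sentence: "The most recent survey data available before the intervention and at the completion of implementation phase will be used for analysis". The study does not run these surveys. Item 3 says the resident data "is routinely collected by the organisation for reporting purposes", and Section 2.10 adds: "Anonymous staff and consumer satisfaction and quality of life surveys are routinely collected for reporting purposes". No interval or fieldwork dates are given.

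Section 2.6.3 fixes the length of the programme: "Implementation of Safewards at each site will occur over 12 weeks".

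Other quantitative measures in Section 2.9 have a dated post period. The study's own staff questionnaire is described as "Surveys (preimplementation and 1 month postimplementation) exploring staff confidence", and the last period for PRN psychotropic use and restrictive-practice events is "3‐months post the completion of the programme". In Table 3, the Effectiveness row lists "pre‐ and postsurveys to assess staff well‐being". The opening of Section 2.9 says that staff well-being will come from routine data, so that entry appears to rest on item 4.

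**The concern.** A pre-post comparison needs a second measurement that reflects exposure to the programme. The rule for items 3 and 4 names the point at which the team looks for the latest survey, but sets no earliest date for the survey it finds. Because the organisation sets the calendar, that survey could have been fielded in the first weeks of roll-out, or before roll-out began. The data are anonymous, so individual records cannot show who had been exposed. The fieldwork date of the wave is the only evidence of exposure.

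The Effectiveness aim in Table 3 is to find outcome measures that are appropriate and feasible and to look for signals of effect, as input to a later trial. A flat result produced by the selection rule could lead the team to discard a usable measure.

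**Working it through.** The article gives no sample size, power or other figure for these outcomes, so there is nothing to reproduce. The check is of timing.

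**Inputs**
- Length of implementation, L = 12 weeks (Section 2.6.3). Section 2.9 calls the same period 3 months.
- Post survey = latest wave available at completion (Section 2.9, items 3 and 4, plain reading).
- Survey interval T: not in the document. Quarterly, six-monthly and annual are assumed to show the range.
- Wave dates are assumed to fall at random relative to the start of implementation, and each wave is treated as a single date.

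**Step 1: latest possible date.** A wave available at completion was collected at or before completion, so exposure at the survey is at most 12 weeks.

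**Step 2: chance that pre and post are the same wave.** The age of the latest wave at completion is uniform between 0 and T. That wave predates the start, and is therefore also the pre wave, with probability max(0, 1 − L/T). Otherwise it falls during roll-out. Mean exposure at the selected wave, counting pre-start waves as zero, is L²/(2T) when T is at least L.

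| Assumed interval | T (weeks) | Same wave, 1 − 12/T | During roll-out, 12/T | Mean exposure, 144/(2T) |
|---|---|---|---|---|
| Quarterly | 13 | 1 − 12/13 = 8% | 92% | 144/26 = 5.5 weeks |
| Six-monthly | 26 | 1 − 12/26 = 54% | 46% | 144/52 = 2.8 weeks |
| Annual | 52 | 1 − 12/52 = 77% | 23% | 144/104 = 1.4 weeks |

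With L taken as 3 calendar months, the same-wave chances are 1 − 3/3 = 0%, 1 − 3/6 = 50% and 1 − 3/12 = 75%.

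**Step 3: waves that do fall in the phase.** When T is at least 12 weeks, such a wave is on average 12/2 = 6 weeks into the roll-out.

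**Step 4: what a post-completion rule would give.** If the post measure is the first wave after completion, the chance that it falls within the 3-month post window already used for the PRN and restrictive-practice data is min(1, 3/T) with T in months: 100% quarterly, 3/6 = 50% six-monthly, 3/12 = 25% annual.

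**The case against.** The strongest reply is that the sentence can be parsed another way: the last survey before the intervention, plus a survey at completion. The Table 3 label "pre‐ and postsurveys to assess staff well‐being" fits that parsing better. A measurement at completion is also not odd in this design, since the fidelity scale is scored then and the PRN and restrictive-practice data have a period that ends there. This much stands: the wording is ambiguous, and a completion time point is not in itself an error. But no text says that the organisation's surveys will be fielded at completion, so under either parsing the available wave may be older.

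Second, the same-wave case needs an interval longer than 12 weeks, and none is stated. That is correct. With quarterly surveys the risk is small (8%, or 0% if the phase is 3 months), and the larger figures rest on assumed intervals.

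Third, this is an uncontrolled feasibility study in two homes that uses routine data for practical and budget reasons, and resident satisfaction and quality of life are not among Table 3's quantitative resident outcomes. Learning whether routine waves are usable is part of its purpose. This limits the consequence. It does not justify a rule that can present an unexposed wave as a post measure.

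A reader might also infer that the survey rule is applied to staff injury, because item 4 includes "staff injury (via the Injury Management platform"). The text does not support that: the timing sentence concerns survey data, and the injury platform is not a survey. A window for injury events may be set in the full protocol or analysis plan.

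**Conclusion.** The point holds as a weakness in a stated rule. On its plain reading, the rule for items 3 and 4 cannot select a survey fielded after completion, and it allows one fielded mid-roll-out or a repeat of the pre wave. The chance of a repeat is about 8%, 54% or 77% for quarterly, six-monthly or annual surveys, given random wave dates and a 12-week phase. The true interval is unknown, so these figures are a range and not an estimate for this study.

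Two stronger conclusions are tempting. One is that the plan will compare a wave with itself; the documents show only that it could. The other is that the results are biased towards no change. That is automatic only when the same wave is used twice. For a wave taken during roll-out it requires that effects build with exposure, which the article does not establish.

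The effect is confined to the routine resident and staff survey comparisons. The PRN, restrictive-practice and study-run staff survey outcomes have their own post timing and are not touched.

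**What to change.** Replace the shared sentence in items 3 and 4 of Section 2.9 with a rule that does the following:

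- Pre survey: the last routine wave fielded wholly before implementation starts at that site.
- Post survey: the first routine wave fielded wholly after completion at that site, within the 3-month post window where one exists.
- Report fieldwork dates for each wave by site.
- Never use one wave as both pre and post.
- If no post-completion wave falls within the project, report the comparison as not evaluable. A wave fielded during roll-out may be shown descriptively, labelled as such.

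This takes a few sentences of text and does not ask the organisation to reschedule anything. The real cost is waiting. The mean wait for the next wave is T/2, or about 6 months for an annual survey, and the project has 12 months in all (Sections 2.2 and 3.3). For an annual survey, only 25% of random schedules put a wave in the 3-month post window, so the outcome may well be not evaluable. In a feasibility study that is itself a result worth reporting.

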**Qualitative Data**
1.In‐depth interviews with up to 12 residents and 12 family members (six from each site) will be conducted approximately 6 months after the commencement of Safewards implementation. Families will be offered to meet face to face in a quiet room in the residential setting, or via telephone to minimise cost and burden We will explore residents' and family members' perspectives and experiences of Safewards.2.Focus groups (with up to eight participants) will be conducted with aged care staff to gain their views on the implementation of Safewards. Three face‐to‐face focus groups will be conducted at each site. Focus group methodology is best suited to gaining views within a collaborative and problem‐solving approach. We will explore experiences of Safewards, barriers and enablers to implementation and any adaptations made to Safewards interventions and sustainability.3.In‐depth face‐to‐face interviews with the aged care organisation leaders will be conducted to gain their views on the implementation of Safewards.4.Steering Committee Meeting Minutes will be reviewed for data pertaining to implementation.

Interviews and focus groups will be conducted by members of the research team and will be audio recorded with permission from participants, to ensure the accuracy of the data capture, and professionally transcribed.

For the qualitative data, a coding reliability approach to thematic analysis will be used to ensure rigour [49]. This will involve the use of a ‘definitive list of codes/themes, a coding label and definition for each code/theme, instructions on how to identify each code/theme, including any exclusions, and examples of each code/theme’ [49, p. 7]. The CFIR codebook will be used to code the data. This includes a description of each domain and sub‐domain and construct definitions to assist coding (https://cfirguide.org/constructs/). Interview and focus group data will be mapped against the CFIR framework domains, with the researchers employing a coding reliability approach to ensure rigour. NVivo 12 will be used to manage data.

### Ethical Considerations

2.10

Ethics was sought from the Flinders University Human Research Ethics Committee to conduct this study. A waiver for consent was sought for de‐identified data including the following: (1) routinely collected data pertaining to psychotropic medication use and restrictive practice incidents (physical, mechanical and environmental restraint); (2) staff satisfaction surveys and (3) consumer satisfaction and quality of life questionnaires.

Data pertaining to psychotropic medication use will be collected and de‐identified by staff from the aged care organisation via an electronic record and/or the psychotropic register. Restrictive practice incidents, documented on internal incident report forms, will be collected and de‐identified by organisational staff. Anonymous staff and consumer satisfaction and quality of life surveys are routinely collected for reporting purposes.

## Discussion

3

Safewards is an evidence‐based programme that provides staff with specific interventions that reduce conflict and restrictive practice use (specifically seclusion) in acute mental health care settings. The Safewards programme (model and interventions) has been successfully implemented in a range of mental health care settings internationally but has not yet been tested in RAC. This study will explore the feasibility of Safewards in reducing restrictive practice use in RAC homes. Given the importance of contextual factors affecting implementation outcomes, this pilot study will apply theoretical frameworks (RE‐AIM and CFIR) to gain an in‐depth understanding of the feasibility and adaptations needed for a future trial to determine effectiveness. The following section explores the knowledge areas that this study seeks to develop.

### Contribution to the Knowledge of Evidence‐Based Interventions to Reduce Restrictive Practices in RAC Homes

3.1

Clinical guidelines prioritise nonpharmacological interventions for people with behavioural and psychological symptoms of dementia [6]. As such, various strategies and interventions have been developed to reduce the use of physical restraints and the overprescribing of psychotropic medication in RAC [18]. Strategies have included education, guidelines, medication reviews, audits, strategies to improve interdisciplinary communication and tips for more personalised care [18]. Although studies that have targeted overprescribing report short‐term improvements, changes are not typically sustained [18].

Overall, there is little evidence on strategies and interventions that have been found to be effective in reducing restrictive practice use in RAC. We suggest that the considerable research on strategies to reduce restrictive practices that has occurred in adult mental health inpatient settings are tested in RAC to assess effectiveness and feasibility. This approach is supported by others, including the Disability Sector. A recent review commissioned by the Australian Royal Commission into Violence, Abuse, Neglect and Exploitation of People with Disability of initiatives to reduce or eliminate the use of restrictive practices acknowledged that most of the evidence on interventions to reduce restrictive practices comes from mental health care settings and encouraged their adoption/trial into the Disability Sector [50]. Cortis et al. [50] identified seven evidence‐based strategies/interventions, which included Safewards. Safewards is broader in its approach than many of the specifically targeted interventions to reduce psychotropic prescribing, identifying six domains which can be the source of conflict and containment (use of restrictive practices) [25]. Adapted for RAC, these domains include the resident community, resident characteristics, regulatory frameworks, the staff team, the physical environment, and outside the care home. By implementing and evaluating Safewards in RAC, this study will contribute to the knowledge about strategies to reduce the range of restrictive practice use (physical, chemical and environmental) in RAC and determine whether adaptations are needed due to contextual differences.

### Contribution to the Knowledge Base for Safewards

3.2

As highlighted, Safewards was designed to reduce conflict and containment in acute mental health care settings [25], with growing interest in exploring its use in other settings [50]. In Australia, for example, the Victorian Safewards trial included three emergency departments and six general health units (https://www.safercare.vic.gov.au/best-practice-improvement/improvement-projects/mental-health-wellbeing/safewards-victoria-trial) and the ACT Safewards trial included two general medical wards and an older persons mental health unit (https://www.health.act.gov.au/safewards). This study will be conducted in a novel context (RAC), with the variation in services across the two sites (residential home care, memory support units and a specialist dementia care unit) providing an ideal setting for this trial.

Recent systematic reviews of published studies of Safewards have included trials that have been conducted in the United Kingdom, Germany, Poland, Denmark, Canada and Australia [22, 51]. These reviews on the effect of Safewards report overall reductions in conflict and containment in general adult mental health units but highlight the need for further rigorous testing of the model in other settings [22, 24]. In addition to examining changes in restrictive practice use and staff experiences, our will study will include the examination of the experiences of residents and family members of Safewards in RAC. Inclusion of services users has been identified as a key priority when trialling interventions (including Safewards) to reduce restrictive practice use [50, 51], although consumer involvement remains infrequent in aged care implementation research [32].

Although there are acknowledged challenges in implementing complex interventions, only one Safewards study has used implementation science to inform programme evaluation. Fletcher et al. [30] conducted a postevaluation of the barriers and enablers of implementation of Safewards across 18 wards in Victoria using the CFIR framework. More recently, two systematic reviews have applied implementation science to examine the implementation of Safewards and other programmes to reduce coercive practices [33, 52]. Björkdahl et al. [52] synthesised the qualitative research on staff experiences of the barriers and enablers to the implementation of Safewards using the i‐PARIHS framework. Lantta et al. [33] examined the use of models, theories and frameworks used in the implementation of the broad range of programmes designed to reduce coercive practices in mental health settings, which included Safewards, but found only nine papers reporting on eight studies met the inclusion criteria [33]. The authors highlighted the variation in selection and use of theories, models and frameworks across the nine implementation studies. The most frequently reported outcomes were acceptability (7/9 papers), appropriateness (8/9) and sustainability (7/9); penetration was the least reported outcome (1/9) [33].

Our research will extend the evaluation of Safewards to RAC and simultaneously contribute to the knowledge base of implementation science in RAC, where there is limited implementation science‐informed research [32]. The CFIR framework was applied to the Victorian Safewards implementation [37], thus using this framework in our current evaluation will allow for a comparison of findings to determine if there are key components across organisations and sectors that facilitate and/or hinder the successful implementation of Safewards.

